| Clinical Study Type            | Single arm interventional cohort study                                                                                                                                                                                                                                                                                                                                                                                                                                                                                                                                                                                                                                              |
| Name of Device                 | Better Therapeutics' Nutritional Cognitive Behavioral Therapy (BT-NCBT-00x)                                                                                                                                                                                                                                                                                                                                                                                                                                                                                                                                                                                                         |
| Sponsor                        | Better Therapeutics, Inc
[name]
[name]                                                                                                                                                                                                                                                                                                                                                                                                                                                                                                                                                                                                    |

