## **9. Sample Size**

The primary study population consists of approximately 20 male and female adult participants (18 – 75 years old), with a diagnosis of nonalcoholic fatty liver disease (NAFLD) or nonalcoholic steatohepatitis (NASH), and who satisfy the inclusion and exclusion criteria. Only those who meet PDFF  $\geq 10\%$  will be included in the primary endpoint analysis.

Sample size calculations are estimated for the primary analysis population, i.e. those who satisfy all inclusion/exclusion criteria and have a baseline PDFF  $\geq 10\%$ .

The sample size was calculated by referencing the mean absolute change in steatosis and standard deviation reported in a 2019 JAMA review of the impact to behavioral weight loss interventions on clinical markers of NAFLD (Koutoukidis et al., 2019). The average mean absolute change in steatosis was -2.4 and mean standard deviation was 1.6. Using these results, it was determined a sample size of approximately 8 participants would provide approximately 90% power, assuming an alpha of 0.05. To account for up to a 20% attrition rate, a minimum of 10 participants are required.

To ensure inclusion of a mix of patients with either NAFLD or NASH, a total of approximately 20 participants will be enrolled. It's expected that up to 50% of fully eligible participants will fail to meet the MRI-PDFF requirements for inclusion in the primary analysis population, resulting in approximately 10 participants included in the primary endpoint analysis. Participants who do not meet the MRI-PDFF requirement for primary analysis endpoint will be included in secondary and exploratory analyses.

Demographics and baseline characteristics will be summarized descriptively for all subjects based on the analysis population. Descriptive summaries will include the number of non-missing observations, mean, median, standard deviation, minimum and maximum for continuous results. Categorical results will be summarized with counts and percentages.

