### 11.1 Primary and Secondary Endpoint Analyses

The primary efficacy endpoint is the change in percent liver fat as measured by MRI-PDFF from baseline to 3 months after enrollment. The results at baseline, at 3 months post-enrollment, and the change from baseline will be summarized descriptively. Change from baseline results will be calculated as (post-baseline minus baseline). The baseline result is defined as the last assessment prior to starting the Better Therapeutics App. In addition, the change from baseline in the percentage liver fat will be tested using a one-sample t-test if the normality assumption is met. The normality assumption will be assessed using the Shapiro-Wilks test for normality. If the normality assumption is not met, then the change from baseline will be tested using a Wilcoxon rank sum test.

The continuous secondary endpoints will be summarized in the same manner as described for the primary efficacy endpoint.

The categorical secondary endpoints, such as the percentage of participants who achieve  $\geq 30\%$  reduction in MRI-PDFF from baseline to post-intervention, will be summarized using counts and percentages. In addition, exact binomial confidence intervals for the true rates will be provided.

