### 11.2 Exploratory Endpoint Analyses

The same statistical methods used to analyze the primary and secondary endpoints will be used to assess the exploratory endpoints. Mean changes in clinical values will be assessed from baseline to 12 weeks after enrollment.

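### The non-normal fallback for the primary endpoint names the Wilcoxon rank sum test, which cannot be run on a single column of paired changes; the signed-rank test is needed

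*Protocol*

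**What the plan says.** The synopsis describes the design as "Single arm interventional cohort study". Section 11.1 defines the tested variable: "Change from baseline results will be calculated as (post-baseline minus baseline". It then gives the main test: "the change from baseline in the percentage liver fat will be tested using a one-sample t-test if the normality assumption is met". The switch between tests is also fixed: "The normality assumption will be assessed using the Shapiro-Wilks test for normality". The fallback follows: "If the normality assumption is not met, then the change from baseline will be tested using a Wilcoxon rank sum test". The synopsis (Statistics, Efficacy Analyses) gives the same rule and the same fallback. The protocol nowhere names a signed-rank test.

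Section 11.1 says the continuous secondary endpoints are summarised in the way set out for the primary endpoint. Section 11.2 goes further for the exploratory endpoints: "The same statistical methods used to analyze the primary and secondary endpoints will be used to assess the exploratory endpoints".

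**The concern.** The one-sample t-test fits the data: one arm, two scans per participant, one difference each. Its nonparametric counterpart is the Wilcoxon signed-rank test, which ranks the absolute changes and uses their signs. The rank sum (Mann-Whitney) test needs two independent samples, and a column of changes has no second sample.

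This is not detail left to the statistical analysis plan. The protocol chooses a test for its primary endpoint, in two places, and names one that does not apply. An analysis plan that follows the text inherits the error, and one that corrects it departs from the protocol. If nobody notices until the Shapiro-Wilk test has rejected, the replacement will be chosen with the data in view. The only way to produce a rank sum p-value would be to compare baseline values with post values as if they came from different people. Between-participant spread in liver fat would then count as noise.

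**Working it through.** **Inputs from the protocol.** Section 9: "The average mean absolute change in steatosis was -2.4 and mean standard deviation was 1.6"; "it was determined a sample size of approximately 8 participants would provide approximately 90% power, assuming an alpha of 0.05". It adds 20% attrition and expects about 10 participants in the primary analysis.

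**Assumptions.** The protocol does not state sidedness; two-sided 0.05 is used. It gives no SD for baseline PDFF, so a range is shown. Changes are taken as independent of baseline.

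**Step 1: the plan's own figure.** The standardised effect is 2.4/1.6 = 1.5. Power of the one-sample t-test comes from the noncentral t distribution with n-1 degrees of freedom and noncentrality 1.5 × √n.

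- n=7: noncentrality 3.97, power 90.8%
- n=8: noncentrality 4.24, power 95.1%
- attrition: 8/(1 - 0.20) = 10

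The stated 8 and 10 reproduce, slightly on the safe side, under a one-sample (paired) test. The sample size therefore assumes the paired analysis.

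**Step 2: is the correct fallback adequate at this size?** The smallest two-sided exact signed-rank p-value is 2/2^n. At n=8 it is 2/256 = 0.0078, so significance is attainable. Simulated power with normal changes is about 92% at n=8 and 98% at n=10.

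**Step 3: rank sum test forced onto baseline versus post values.** Simulation, n=8, normal changes with mean -2.4 and SD 1.6:

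| Assumed baseline SD (PDFF points) | Signed-rank | Rank sum |
|---|---|---|
| 1.6 | about 92% | 66% to 72% |
| 3 | about 92% | 20% to 30% |
| 5 | about 92% | 4% to 7% |
| 7 or more | about 92% | about 2% or less |

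The ranges reflect the assumed shape of the baseline. A right-skewed baseline (10 plus a gamma variable) gives the higher values and a symmetric one the lower. The rank sum test had less power in every setting.

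**Step 4: how often this would matter.** The loss occurs only if Shapiro-Wilk rejects, so the power of the whole two-step rule at n=8 is the relevant figure.

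- Normal changes: the fallback is triggered in about 5% of trials. Power falls from about 95% to about 90% to 94%, depending on baseline SD.
- Exponential-shaped changes, same mean and SD, long tail towards larger reductions, baseline SD 5: the fallback is triggered in about a third of trials. Power falls from about 100% to about 70%. As a rough check, with 34% triggered and rank sum power of 3% to 7%, 0.66 × 100% + 0.34 × (3% to 7%) is about 67% to 68%. At n=10 the trigger rate is about 44% and power is about 60%.
- The same shape with the tail reversed, baseline SD 5: power falls from about 84% to 86% with signed-rank as fallback, to about 60% to 66%.

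**The case against.** The strongest reply is that this is a slip of the pen. The fallback sentence takes the change from baseline as its object, the preceding test is one-sample, and a rank sum procedure needs a grouping variable that this column lacks. An analyst would notice at once. Section 11 calls itself a general approach, and the statistical analysis plan, not shown here, may already name the signed-rank test. All this is plausible and makes the damaging use of the test unlikely. It does not make the protocol text right.

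A reader might infer that the plan would lose nearly all its power. The documents do not support that. If the test cannot be run on the changes, no power is lost because nothing is computed. If it is run on raw values instead, near-total loss needs a baseline SD of about 4 points or more, and the protocol gives no such figure. With normal changes the two-step rule still has roughly the stated 90% power, because the fallback is rarely reached.

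The first skewed scenario also favours the criticism. Each change equals -2.4 - 1.6 × (E - 1) with E ≥ 0, so none exceeds -2.4 + 1.6 = -0.8. No participant stays stable or worsens, and signed-rank power is close to 100% by construction. The reversed tail is the fairer companion and shows a loss of about 20 points or a little more.

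Nor does the text clearly carry the test to every continuous secondary endpoint, since Section 11.1 speaks there only of summarising. Section 11.2 is explicit for the exploratory endpoints.

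**Conclusion.** The named fallback is wrong for this endpoint and should be corrected. That conclusion rests only on the text: one arm, one column of paired differences, a one-sample main test and a two-independent-sample fallback. It needs no assumption.

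The size of the harm is conditional on three things: that Shapiro-Wilk rejects, that the test is then run literally on baseline and post values, and the baseline SD, which is assumed here. Under those conditions the loss at n=8 runs from about 20 points (92% to 72%) at SD 1.6 to about 90 points at SD 7 or more. Averaged over the two-step rule, it is about 1 to 5 points with normal changes and about 20 to 30 points in the two skewed settings examined. Those skewed settings are illustrations, not forecasts.

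**What to change.** In Section 11.1 and in the Efficacy Analyses part of the synopsis, replace the rank sum test with the Wilcoxon signed-rank test of the paired changes, preferably with exact p-values at this sample size. Section 11.2 then carries the corrected method to the continuous exploratory endpoints. Section 11.1 does the same for the continuous secondary endpoints if they are to be tested; one added clause could say whether they are. Make the change before outcome data are examined, and check that the statistical analysis plan agrees.

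The cost is a change of wording in two places. No new data and no change in sample size are needed. Replacing the Shapiro-Wilk switch with one fixed test, or reporting a Hodges-Lehmann estimate beside the signed-rank test, would be optional improvements and are not needed to correct this error.

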### 11.2 Exploratory Endpoint Analyses

The same statistical methods used to analyze the primary and secondary endpoints will be used to assess the exploratory endpoints. Mean changes in clinical values will be assessed from baseline to 12 weeks after enrollment.

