| Indication under investigation | Better Therapeutics' BT-NCBT-00x is a software program intended to help patients with NASH/NAFLD, under the guidance of their physician, improve biometric markers. The BT-NCBT-00x software delivers nutritional cognitive behavioral therapy to patients via a mobile application (App) that targets behaviors related to improving cardiometabolic disease.                                                                                                                                                                                                                                                                                                                      |
| Objective(s)                   | 
The primary objective is to evaluate the feasibility and efficacy of BT-NCBT-00x in improving liver health in patients diagnosed with nonalcoholic fatty liver disease (NAFLD) or nonalcoholic steatosis (NASH).
 
The secondary objective is to gather user-experience feedback that will be used to improve usability of BT-NCBT-00x for future use in patients with NAFLD/NASH and evaluate intervention safety in this patient population.
 
In addition, this study will explore the degree to which various non-invasive imaging technologies, composite scores, and serum laboratory biomarkers are sensitive to behavioral changes induced by BT-NCBT-00x.
 |

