|  | 
Using these results, it was determined a sample size of approximately 8 participants would provide approximately 90% power, assuming an alpha of 0.05. To account for up to a 20% attrition rate, a minimum of 10 participants are required.
 
To ensure inclusion of a mix of patients with either NAFLD or NASH, a total of approximately 20 participants will be enrolled. It's expected that up to 50% of fully eligible participants will fail to meet the MRI-PDFF requirements for inclusion in the primary endpoint analysis, resulting in approximately 10 participants included in the primary endpoint analysis. Participants who do not meet the MRI-PDFF requirement for primary analysis endpoint will be included in secondary and exploratory analyses.
 
Demographics and baseline characteristics will be summarized descriptively for all subjects based on the analysis population. Descriptive summaries will include the number of non-missing observations, mean, median, standard deviation, minimum and maximum for continuous results. Categorical results will be summarized with counts and percentages.
 
Efficacy Analyses
 
The primary efficacy endpoint is the change in percentage liver fat as measured by MRI-PDFF from baseline to 3 months after enrollment in those with a baseline PDFF <math>\geq 10\%</math>. The results at baseline, at 3 months post-enrollment, and the change from baseline will be summarized descriptively. In addition, the change from baseline in the percentage liver fat will be tested using a one-sample t-test if the normality assumption is met. If the normality assumption is not met, then the change from baseline will be tested using a Wilcoxon rank sum test.
 
The continuous secondary and exploratory endpoints will be summarized in the same manner as described for the primary efficacy endpoint.
 
The categorical secondary and exploratory endpoints, such as the percentage of participants who achieve <math>\geq 30\%</math> reduction in PDFF from baseline to post-intervention, will be summarized using counts
 |

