Skill exercises are intended to provide an opportunity for participants to practice skills related to behavioral beliefs. The method by which participants must practice these skills is designed to enhance executive function tasks such as planning, problem solving and goal setting. Each lesson explains the rationale and benefits of the skill exercise in reference to the core topic being explored.

In addition to completing a lesson (and one or more skill exercises), BT-NCBT-00x directs patients to self-report diet and exercise behaviors, medication adherence, and biometrics (e.g., weight). If the patient has comorbid Type 2 diabetes or hypertension, he or she will also be able to self-monitor fasting blood glucose and blood pressure each day. Weekly behavioral goals, including diet and exercise behaviors, are determined through a goal setting exercise, and are advanced in a manner most likely to maintain or increase self-efficacy. When self-efficacy is high, the participant has a high probability of achieving his or her goals.

Participants will be directed to engage with one lesson each week of the study, to report plant-based meals consumed and minutes of exercise completed and, if indicated, to measure

their blood glucose and/or blood pressure daily. All participants will be given access to the App for 3-months.

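### The objective on markers' sensitivity to behavioral change is analysed without any behavior variable, so the planned summaries show change during App use but cannot link it to behavior

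*Protocol*

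**What the plan says.** The Protocol Synopsis (Objective(s)) lists, after the primary and secondary objectives, an exploration of "the degree to which various non-invasive imaging technologies, composite scores, and serum laboratory biomarkers are sensitive to behavioral changes induced by BT-NCBT-00x".

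Section 11.2 gives the analysis of the exploratory endpoints in two sentences: "The same statistical methods used to analyze the primary and secondary endpoints will be used to assess the exploratory endpoints" and "Mean changes in clinical values will be assessed from baseline to 12 weeks after enrollment". The methods carried over are those of section 11.1. For a continuous endpoint they are descriptive summaries, and for the primary endpoint also a test: "the change from baseline in the percentage liver fat will be tested using a one-sample t-test if the normality assumption is met", with a Wilcoxon test otherwise. For a categorical endpoint they are counts and percentages, and "exact binomial confidence intervals for the true rates will be provided". The synopsis words the continuous case more softly: "The continuous secondary and exploratory endpoints will be summarized in the same manner as described for the primary efficacy endpoint".

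Section 5.4 shows that behavior is recorded. Participants complete weekly lessons in the App and are directed "to report plant-based meals consumed and minutes of exercise completed". In the analysis sections this information appears once, in section 10, where a minimum number of lessons defines the Per Protocol population.

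The study has a single arm. Section 5.1 makes a CAP score below 300 dB/m a screen failure, and CAP is also one of the exploratory markers in section 3.3.

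**The concern.** The objective asks about a link between two things, behavior and a marker. The analysis fixed for it uses only one of them, the marker. A mean change from baseline shows that a marker moved in the group. It does not show whether it moved in the participants who changed what they ate or how much they exercised.

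With no control arm, other explanations stay open. One is built in for CAP: participants enter because their CAP is high, so a lower second reading is expected from regression to the mean alone. Usual medical care also continues throughout treatment and can move markers.

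The objective also speaks of degree, which invites comparison between markers. Raw changes in dB/m, kPa and IU/L do not by themselves provide one. Section 1 says the study is meant to help plan future studies, so a marker wrongly labelled as sensitive to behavior could be carried forward.

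**Working it through.** **1. Does behavior enter any endpoint or analysis?**

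| Place in the protocol | Content | Behavior variable? |
|---|---|---|
| Synopsis, exploratory endpoints; section 3.3 | Changes and responder percentages for CAP, stiffness, weight, ALT and FAST (HbA1c in the synopsis only); surveys | No |
| Synopsis, Statistics; sections 11 and 11.1 | Summaries, test of change in liver fat, exact intervals | No |
| Section 11.2 | Same methods, mean changes | No |
| Section 10 | Minimum lessons for Per Protocol | Only to define a population |
| Section 5.4 | Meals, exercise minutes and lessons recorded in the App | Recorded, not analysed |

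**2. The plan's own figure.** Section 9 gives a mean change of -2.4 and an SD of 1.6, so the standardized change is 2.4/1.6 = 1.5. Exact two-sided one-sample t-test power at alpha 0.05 is 90.8% at n=7 and 95.1% at n=8. The stated 8 for about 90% power is adequate, and 8/(1 - 0.2) = 10 matches the stated minimum. The sample size is not in dispute here.

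**3. Does a mean-change test respond to the marker-behavior link?** Write the standardized marker change as M = s + ρB + √(1 - ρ²)·e, with B (behavior, centred) and e independent standard normal. Then M has mean s and variance ρ² + (1 - ρ²) = 1, whatever ρ is. At a given mean shift s the test result therefore does not depend on ρ. Simulation with 40,000 runs agrees: at n=20 and s = 0.8, the test flags the marker in 92% of trials with ρ = 0 and 92% with ρ = 0.7.

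**4. Illustration of the size.** Assume s = 0.5 and ρ = 0. Power is P(|T| > t) with n - 1 degrees of freedom and noncentrality s√n. Section 9 plans about 20 participants. Applying its 20% attrition to all of them (an assumption, since it is stated for the primary population) leaves 20 × 0.8 = 16.
- n=20: noncentrality 0.5 × √20 = 2.24, critical value 2.09, flagged in about 56.5% of trials.
- n=16: noncentrality 0.5 × √16 = 2.00, critical value 2.13, flagged in about 46.5%.

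Over a range of assumed shifts:

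| Assumed shift (SD) | n=16 | n=20 |
|---|---|---|
| 0.3 | 20% | 25% |
| 0.5 | 46.5% | 56.5% |
| 0.7 | 74% | 84% |
| 0.8 | 85% | 92% |

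The documents give no shift for these markers. The table describes how a test behaves and predicts nothing about this trial.

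**5. What a direct estimate of the link could deliver.** By Fisher's transformation, atanh(0.5) = 0.549. At n=16 the half-width is 1.96/√13 = 0.544, so the 95% CI for r = 0.5 runs from tanh(0.006) = 0.01 to tanh(1.093) = 0.80. At n=20 it is 0.07 to 0.77. The correlation detectable with 80% power is about 0.65 at n=16 and 0.59 at n=20. This supports estimation, not confirmation.

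**The case against.** **The objective states no null hypothesis.** A reader might infer that the plan tests for no relation between marker and behavior with an inflated error rate. The documents do not support that. The objective only says the study will explore, and section 2 states a different hypothesis: other markers of liver health improve. Mean change matches it. The percentages in the table above are ordinary power to detect a real shift. This stands, and the point must not be put as a type I error problem.

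**Sensitivity can mean responsiveness.** If it only means that the marker moves over the intervention, change summaries are a usual first analysis. That is a fair reading, but the objective ties sensitivity to behavioral changes, and a single arm cannot make that attribution.

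**A reader might infer that markers which track behavior will be missed.** This holds only if the mean shift is small. The protocol's one planning effect, for steatosis, is 1.5 SD. Even at 0.75 SD the test has 80% power at n=16 and 89% at n=20. If the App moves behavior and marker substantially on average, the mean change will show it. A claim that correlation has far better power is not supportable either, because it assumes behavior measured without error. With an assumed correlation of 0.6, power is 73% at n=16 and 83% at n=20 for error-free behavior, but 39% and 48% in a simulation with an assumed reliability of 0.5.

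**Testing of exploratory endpoints is uncertain.** It rests on one sentence in section 11.2; the synopsis says they are summarized, and categorical endpoints get intervals only. This stands, but behavior is absent on either reading.

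**Comparison across markers is not wholly absent.** Responder percentages share a scale, although their thresholds are not equivalent, and means and SDs of change are already planned. This stands: a common scale needs only one further ratio.

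**The SAP may add the analysis.** Section 11 calls its text a general approach and defers detail to a SAP not seen here. That lowers the weight of the point. It remains because section 11.2 does name a method, and that method does not address the objective.

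**Conclusion.** The mismatch is real and modest. The objective concerns sensitivity to behavioral change, while the analysis fixed in section 11.2 contains no behavior variable and, without a control arm, cannot distinguish behavior-linked change from regression to the mean or usual care. That conclusion rests on the protocol text alone. Its numerical size does not: the figures of about 56.5% and 46.5% depend on an assumed 0.5 SD shift unrelated to behavior, normal data, and exploratory endpoints actually being tested two-sided at 0.05.

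The planned summaries are suitable for the section 2 hypothesis and should stay. The primary endpoint and the sample size are unaffected. For an exploratory objective in a feasibility study of about 20 participants, this is an inexpensive improvement rather than a defect that threatens the trial.

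**What to change.** In section 11.2 (and the SAP), for each marker covered by the objective:

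1. Report the standardized response mean (mean change divided by SD of change) with a 95% CI, on the same participants for all markers.
2. Report a Spearman correlation with a 95% CI between the change in the marker and one prespecified App-recorded behavior measure during treatment, for example exercise minutes, plant-based meals or lessons completed. Label it exploratory estimation. State that it reflects behavior level during treatment, because Table 1 schedules no pre-treatment behavior measure. Limiting it to one measure avoids a large grid of correlations with chance findings. Correlation with change in MRI-PDFF may be added as concordance with the reference imaging measure, but it is not evidence on behavior.
3. State that a nonzero mean change alone will not be read as sensitivity to behavioral change.

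Name the markers explicitly, since HbA1c is in the synopsis list but not in section 3.3. Alternatively, reword the objective as describing marker change during App use and leave the analysis as it is.

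The cost is a few lines of text and a small analysis of data already collected. The drawbacks are that App behavior is self-reported and may be sparse in participants who stop using it, and that intervals at n of 16 to 20 are too wide to rank markers firmly.
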